**Influenza immunity**	
Whether the individual already has acquired some immunity against influenza through previous influenza vaccinations or a previous influenza infection.	We will consider: (1) Whether the individual has received an influenza vaccination in the previous year. (2) Whether the individual has experienced an influenza infection in the previous year.

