The target trial for the influenza vaccine is very similar, but differs slightly due to the seasonality of the disease. Influenza viruses are constantly mutating, necessitating yearly changes of the influenza vaccines. It is therefore recommended to estimate influenza vaccine effectiveness on a seasonal basis instead (30). The target trial is therefore also defined on a seasonal basis, meaning that there is one target trial per influenza season that should be emulated. Recruitment would start each year on the first of September. People may then be recruited and followed up until the end of May of the next year (31.05.).

Both target trials are pragmatic, in the sense that no placebo control is used. We choose to formulate them this way because it is generally impossible to emulate placebo-controlled randomized controlled trials using only observational data (27). We further assume perfect adherence, so that every individual randomized to the treatment group actually receives the respective vaccination strategy and every individual in the control group does not. Our main interest is therefore in the *per-protocol* effect, although we will also estimate *intention-to-treat* effects in a sensitivity analysis, as described in detail in Section 2.6.3. Because we compare the vaccine effectiveness of patients with autoimmune diseases and other patients, but are unable to randomize the disease status itself, we are interested mainly in the *effect modification* of the disease status on the vaccine effectiveness (31). The result is a comparison of two population-based total causal treatment effects (32).

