### 2.3 Study design and data source

Routinely collected claims data from a large German statutory health insurance (BARMER) will be used to carry out the study. BARMER is the second largest statutory health insurance in Germany with about 8.6 million insured individuals (status of 2024). BARMER claims data are available on application for research purposes in anonymized data sets, hosted in a scientific data warehouse [in German: Wissenschaftliches Data Warehouse (WDWH)] by BARMER. Within the project VAC-MAC (in german: VACcinierung von MS/Arthritis/Colitis-Patient:innen, DRKS-ID: DRKS00031559, registered 28.08.2023), we have access to data from 2013 to 2021. VAC-MAC is a project funded by the German Innovations Fund (Innovationsfonds, grant number 01VSF21044) with multiple goals related to assessing and improving the vaccination coverage of individuals with MS, IBD, or CIRD.

The target population of all target trials consists of all individuals insured by the BARMER who fulfill the following inclusion criteria. The subject:

Has been enrolled in the BARMER health insurance company for at least 2 years before inclusion into the study with interruptions of no more than 5% of the total time.Is at least 18 years old at the start of observation.Has a biological sex of either male or female.Did not receive an organ transplantation in the last 2 years before inclusion into the study.Did not have any form of cancer in the last 2 years before inclusion into the study.Did not have an autoimmune-related disease other than MS, IBD, or CIRD in the last 2 years before inclusion into the study.

The start of the observation period/study is defined as the date on which an individual is included in the study during the trial emulation, as outlined in Section 2.6. In addition to these criteria, we also define one trial-specific inclusion criteria for each vaccine-effectiveness analysis. For the herpes zoster vaccine-effectiveness study, we require that the individual has not previously received a herpes zoster vaccination. Similarly, for the influenza vaccine-effectiveness trials, we require that the individual has not already received an influenza vaccination in the current influenza season.

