A detailed list of all International Statistical Classification of Diseases and Related Health Problems (ICD)-10 Codes used to assess the inclusion criteria is given in the online supplement. We require two years of previous enrolment in the BARMER because we would otherwise be unable to obtain information on all relevant confounders as described in Section 2.5.4. In these 2 years of enrolment, small interruptions are allowed (up to 5% of the total time), as a compromise between the potential for misclassification that arises, because no information is recorded when a person is not insured at BARMER, and the available sample size. The studies are further constrained to contain only biological males and females due to small amounts and inconsistent coding of the “diverse” category in the BARMER data. People with cancer, previous organ transplantations and other autoimmune diseases are excluded due to the effect these conditions and/or their treatment have on the immune system. There are no other exclusion criteria in this study. Special populations, such as pregnant women and people with other chronic or life-threatening diseases are also eligible to be included in the study.

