**HZ immunity (Herpes Zoster immunity)**	
Whether the individual already has acquired some immunity against herpes zoster through a previous infection.	An indicator of whether the individual has experienced a medically attended herpes zoster infection in the previous six month will be used.

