**Vaccination plan**	
For individuals with MS, IBD, or CIRD it is not unusual that the vaccination is planned in advance by the physician and aligned with changes in medication that may have immunosuppressive effects. For example, the physician may decide that the individual should be vaccinated next week. To allow the patients immune system to make a proper response to the vaccination, a new prescription of immunosuppressive medication is then delayed for a few weeks. This variable states whether such a plan was made or not.	An indicator of whether a person receives a medication change shortly after vaccination may be created. However, this type of indicator breaks the time-line, since information from the future would be used. We will perform an additional sensitivity analysis to determine the effect of using this indicator as an adjustment variable.

Using this DAG and the *backdoor criterion* (47), we then identified separate sets of factors that we need to adjust for in each vaccine effectiveness analysis (53). These sufficient adjustment sets are very similar. In both of the two considered analyses, we will adjust for *Age, Sex, Place, Calender Time, Cautiousness, Disease Status, Healthcare-Seeking Behavior* (HSB), *Treatment, Health Status*, and *Vaccination Plan*. The only differences are that we additionally have to adjust for *Chicken Pox* and *Herpes Zoster Immunity* in the herpes zoster vaccine effectiveness analysis and that we also have to adjust for *Influenza Immunity* in the influenza vaccine effectiveness analysis.

Note that, given our assumptions, there is no need to adjust for socioeconomic status in either analysis, because we hypothesize that the effect of this variable on each outcome is only indirect and is thus already adjusted for by including the other variables. It is also not strictly necessary to adjust for sex in the influenza vaccine effectiveness analysis for the same reason. We choose to include sex anyway, because it can be seen as a proxy for other relevant confounders such as cautiousness that we may not be able to fully adjust for given the mentioned indicators (48).

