#### 2.6.1 Matching method

Due to the different target trials per vaccine of interest, the planned matching and analysis strategy also differs slightly. To analyze the effectiveness of the herpes zoster vaccine, a single matching process will be used. For the influenza vaccine effectiveness trials we will use the same procedure, with the only difference being that it will be performed separately for each influenza season. The matching will be carried out as follows.

For the previously defined start date of the respective trial, the eligibility of all individuals contained in the BARMER database will be determined using the above mentioned inclusion criteria. Eligibility will be checked using only the information available at that time. Every individual who was vaccinated with the vaccine of interest on this date is subsequently included in the dataset, in the treatment group. For every individual included in this way, we then include *k* further individuals who fulfill the inclusion criteria, but have not been vaccinated yet, in the control group. These controls will be matched exactly by age in years, gender, place of residence and disease group. If more than *k* potential controls are identified for a case, *k* controls will be picked at random from these. We will try to include 2 controls per case first (*k* = 2), but will lower this number to 1 if the number of available matches is insufficient. The date of inclusion equals “time zero” (27) for all individuals. Information about all relevant confounders is recorded as available on this date, corresponding to baseline information. This procedure is repeated on all subsequent days, until the emulated trial is over.

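### Table 2 leaves the window for prior influenza vaccination open; read as 365 days before entry it misses about half of habitual vaccinees, and the zoster analysis does not use this variable

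*Protocol article*

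**What the plan says.** Table 2 of the protocol article gives two indicators of influenza immunity, one for vaccination and one for infection. The vaccination indicator is "Whether the individual has received an influenza vaccination in the previous year", and the infection indicator uses the same window. Neither says whether the year is a rolling 365 days, a calendar year or an influenza season.

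Section 2.6.1 fixes when covariates are measured: "Information about all relevant confounders is recorded as available on this date, corresponding to baseline information". For a vaccinated person that date is this season's vaccination date, and the matched control takes the same date. Each influenza trial runs from 1 September to 31 May (Section 2.2: "Recruitment would start each year on the first of September"). Eligibility requires that "the individual has not already received an influenza vaccination in the current influenza season" (Section 2.3). On the data held, Section 2.3 states: "We require two years of previous enrolment in the BARMER because we would otherwise be unable to obtain information on all relevant confounders".

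Section 2.5.4 limits the immunity adjustment to one analysis: "we also have to adjust for *Influenza Immunity* in the influenza vaccine effectiveness analysis". The zoster analysis adds chickenpox and zoster immunity instead. The healthcare-seeking indicators common to both analyses are two counts of physician visits, pneumococcal vaccination in the two years before entry, and a preventive check-up. Influenza vaccination is not among them, although Section 2.5.2 identifies it from reimbursement codes.

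**The concern.** People who are vaccinated every autumn do not attend on the same day each year. If the look-back is 365 days from this season's vaccination, someone who attends a week later than last year is coded as not vaccinated in the previous year. The indicator then partly measures how early a person entered the season, not whether that person was vaccinated last season. The error also differs by arm, because a habitual vaccinee serving as a control is, by construction, not yet vaccinated on the matching date.

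Past influenza vaccination marks both residual immunity and vaccination habit, and it is already in the claims. Measuring it poorly would weaken the adjustment in all four influenza trials. Leaving it out of the zoster analysis gives up a recorded vaccination behaviour, although the plan accepts pneumococcal vaccination as a proxy for the same concept.

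**Working it through.** **Plan's own figure.** The article states no capture rate, so there is none to reproduce.

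**Inputs from the article.** Season 1 September to 31 May; covariates dated at inclusion; at least two years of prior enrolment; data from 2013; first influenza trial from September 2015.

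**Inputs assumed (not in the documents).** Vaccination dates roughly normal with mean about 20 October, SD 15–35 days, correlation between consecutive seasons 0–0.8, and a shift between seasons of −7, 0 or +7 days.

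**Step 1: rolling 365 days.** Let p be last season's vaccination day and c this season's, each counted from 1 September. The gap is c + 365 − p, so the dose is missed when c > p. If the two dates are exchangeable, P(c > p) is just under 0.5 at any correlation, the shortfall being same-day ties. Simulation over the assumed range gives:

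| Shift this season | Habitual vaccinees missed |
|---|---|
| none | 48–50% |
| 7 days earlier | 22–45% |
| 7 days later | 55–75% |

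**Step 2: dependence on entry date and arm.** With no shift, about 5–29% of September entrants are missed, against about 71–100% of those entering after November. Habitual vaccinees who serve as not-yet-vaccinated controls are missed in 13–33%, against 48–50% among the vaccinated.

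**Step 3: other readings.**
- *Previous calendar year:* 0–5% missed. The loss arises only where this season's entry or last season's dose falls in January to May. For a January–May entrant, the previous calendar year contains the current season's autumn, where an eligible person has no dose by definition, and it omits the autumn before.
- *Previous influenza season:* 0% missed, by definition.
- *Two-year look-back:* 0% missed. The largest possible gap runs from 1 September of last season to 31 May of this one: 365 + 272 = 637 days, below 730.

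**Step 4: can the bias be sized?** Assume a true null effect, habit prevalence of 80% in the vaccinated and 20% in controls, an indicator that catches half of habitual vaccinees in both arms, and no other covariates. For a habit–outcome risk ratio r, the unadjusted bias is (1 + 0.8(r − 1)) / (1 + 0.2(r − 1)). Among those coded negative, habit prevalence is 0.8 × 0.5 / (1 − 0.4) = 0.667 in the vaccinated and 0.2 × 0.5 / (1 − 0.1) = 0.111 in controls. Standardising to the vaccinated:

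- r = 1.25: unadjusted 1.20 / 1.05 = 1.14; adjusted (0.4 × 1.25 + 0.6 × 1.167) / (0.4 × 1.25 + 0.6 × 1.028) = 1.200 / 1.117 = 1.08 (1.075 before rounding).
- r = 0.8: unadjusted 0.84 / 0.96 = 0.875; adjusted (0.4 × 0.8 + 0.6 × 0.867) / (0.4 × 0.8 + 0.6 × 0.978) = 0.840 / 0.907 = 0.926.

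A complete indicator gives 1.00 in both cases. The direction changes with r, and the article supplies neither r nor the prevalences. This shows the mechanism; it does not estimate the bias.

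**Step 5: zoster analysis.** No arithmetic applies. Section 2.5.4 places healthcare-seeking behaviour in the zoster adjustment set, and Table 2 measures it by proxies, one of them a vaccination. Influenza vaccination is recorded from the same kind of claims and is not used.

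**The case against.** The strongest objection is that the article never says 365 days. Where Table 2 ties a one-year window to entry (physician visits), it refers to the year before study entry. The different wording here could mean a calendar year or a season, and the online supplement, which is not shown, may settle it. This stands in part: the loss of about half is conditional and cannot be stated as a fact about the plan. But covariates are dated at inclusion, and the next row of Table 2 uses the parallel form "experienced a medically attended herpes zoster infection in the previous six month", which is hard to read as anything but a look-back from entry. In Table 2 the treatment row refers to the supplement; the immunity rows do not.

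A reader might infer that capture is close to complete for early entrants and close to nil for late ones. That is the extreme of the gradient. With correlation 0.8, a person entering two SDs late is still captured with probability P(Z > 0.4/0.6), about 25%.

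A reader might also infer a spurious effectiveness of some size. The documents do not support one. The plan matches exactly on age, sex, place and disease group, aligns inclusion dates, and adjusts for visits, pneumococcal vaccination, check-ups, comorbidity, hospital stays and care level. What remains after that is unknown. The plan concedes residual confounding and adds urinary tract infection as a negative control outcome. That can reveal health-seeking bias, but it neither corrects it nor shows confounding through influenza-specific immunity.

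On zoster, the adjustment set comes from a causal graph whose figure is not shown, and healthcare-seeking behaviour already has four indicators. The gain from a fifth cannot be quantified. It needs no change to the graph, however, because it is only another measurement of a concept already in the set.

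Finally, two years of look-back might suggest that six months is too short for prior zoster. Holding the data does not show that a longer window measures zoster immunity better, and no change is asked for there.

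**Conclusion.** The point holds in conditional form. The window is not fixed. On its most natural reading it misses about half of habitual vaccinees under stable timing (22–75% with a one-week shift), increasingly so for later entrants and unequally between arms. These figures rest on assumed vaccination dates. On a calendar-year reading the loss is 0–5%, and on a seasonal reading there is none. Only the seasonal reading is sound throughout, and it fits the plan's own season-by-season trials, but the text does not state it. The resulting bias in vaccine effectiveness has no derivable size or sign.

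The absence of prior influenza vaccination from the zoster adjustment holds whatever the window. It is a missed improvement at almost no cost, of unknown size.

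**What to change.** 1. Define the vaccination indicator as influenza vaccination in the previous influenza season (1 September to 31 May), irrespective of inclusion date.
2. Define prior influenza infection as any medically attended influenza from the start of the previous season up to time zero. Limiting it to the previous season would drop infections earlier in the current season, which do not exclude a person and do bear on immunity.
3. In the zoster analysis, add influenza vaccination in the 24 months before inclusion to the healthcare-seeking indicators, alongside pneumococcal vaccination.

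All three use data already held. The windows in items 1 and 2 reach back at most 637 days, inside the two-year enrolment requirement, and item 3 uses exactly that guaranteed period. For the first influenza trial (from September 2015) the previous season began in September 2014, within data that start in 2013. The cost is recoding and one extra covariate in the zoster model.

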**HZ immunity (Herpes Zoster immunity)**	
Whether the individual already has acquired some immunity against herpes zoster through a previous infection.	An indicator of whether the individual has experienced a medically attended herpes zoster infection in the previous six month will be used.

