### 2.4 Study period

Although information between 2013 and 2021 is available, we will not use this entire duration as a study period for all of the target trial emulations. First, as described in Section 2.2, there will be one trial emulation per influenza season, with only the time during the respective season being included. Secondly, the first influenza vaccine effectiveness trial emulation will start with the influenza season of 2015/2016 and not with influenza season of 2013/2014, because we need two years of previous follow-up to determine eligibility of the individual and to measure the relevant confounders. Finally, although information for a fifth trial emulation in the influenza season of 2019/2020 would be available, we will not perform this analysis. The reason for this decision is that the COVID-19 pandemic started during this season and largely overshadowed the influenza season of this year. The likely large amounts of underreporting of influenza infections during the COVID-19 pandemic, combined with the actual effects of the pandemic and the measures taken to combat it (33), make a target trial emulation infeasible. Similarly, the target trial for the herpes zoster vaccine effectiveness analysis only starts on the 01.12.2018, because the inactivated herpes zoster vaccine was not available in Germany and not recommended by the STIKO (in German: “Ständige Impfkommission”) before this date (29).

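### Prior zoster, a required confounder, is measured over six months although two years of claims are guaranteed, so avoidable residual confounding may remain in zoster vaccine effectiveness

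*Protocol article*

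**What the plan says.** Table 2 of the protocol article describes the herpes zoster immunity node as "Whether the individual already has acquired some immunity against herpes zoster through a previous infection", with no limit on how long ago. The indicator in the same row is narrower: "An indicator of whether the individual has experienced a medically attended herpes zoster infection in the previous six month will be used".

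Section 2.5.4 makes the node part of the sufficient adjustment set: "we additionally have to adjust for *Chicken Pox* and *Herpes Zoster Immunity* in the herpes zoster vaccine effectiveness analysis".

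Section 2.3 lists as an inclusion criterion that the subject "Has been enrolled in the BARMER health insurance company for at least 2 years before inclusion into the study", and gives the reason: "We require two years of previous enrolment in the BARMER because we would otherwise be unable to obtain information on all relevant confounders". It also states that "we have access to data from 2013 to 2021", while Section 2.4 says the zoster trial "only starts on the 01.12.2018".

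Section 2.5.4 concedes that baseline zoster immunity will probably be underestimated and that residual confounding may follow. It attributes this to infections that never reached a physician and to the limited data years. For quantification it points to Section 2.6.6, where the only analysis is the urinary tract infection negative control outcome.

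**The concern.** The construct has no time limit, but its indicator covers a quarter of the history that every participant must have. Someone with treated zoster eight months before entry is coded the same as someone with no recorded episode.

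The design can produce such people itself. Prior zoster is not an exclusion, and Section 2.6.1 lets a control who is later vaccinated re-enter in the treatment group. A control who has zoster during follow-up and is vaccinated more than six months later re-enters as having no prior zoster.

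By the protocol's own causal graph, incomplete adjustment for this node leaves a backdoor path partly open. If an episode 7 to 24 months ago affects both the decision to vaccinate and the risk of a later zoster claim, the zoster VE carries bias that a longer look-back would reduce. Matching on age, sex, residence and disease group does not address it directly.

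**Working it through.** The plan gives no figure on this point, so there is none to reproduce. Two checks apply.

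**1. Share of the guaranteed history that is used**

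Inputs: a 6-month look-back (Table 2) and 24 months of guaranteed enrolment (Section 2.3), with gaps of at most 5%, or 0.05 × 730 = 36.5 days.

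- Window used: 6/24 = 25%.
- Window not used: 18/24 = 75%. If attended episodes occur at a constant rate, this is the share of episodes in the guaranteed window that is coded as none.
- From 01.01.2013 to 01.12.2018 is about 71 months. For people insured throughout, the indicator covers 6/71 = 8.5% of the history held at trial start.

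Other look-backs in Table 2, for comparison:

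- Two years: pneumococcal vaccination, check-up, hospital stays.
- One year: physician visits, comorbidity index, treatment category, prior influenza infection and vaccination.
- Six months: zoster history, the shortest stated.

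**2. Possible size of the bias**

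The standard factor for an unadjusted binary confounder, acting on the relative risk, is

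B = [1 + p1(HR − 1)] / [1 + p0(HR − 1)], with observed VE = 1 − (1 − true VE) × B.

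Here p0 and p1 are the proportions of unvaccinated and vaccinated people with an attended episode 7 to 24 months ago, and HR is the effect of such an episode on a new zoster outcome. None of these is in the documents. The assumed ranges are 5 to 30 attended episodes per 1000 per year (p0 = rate × 18/12, so 0.75% to 4.5%), an odds ratio (OR) of vaccination given such an episode of 0.5 to 4, and HR 0.3 to 3.

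| Rate per 1000 per year | OR | HR | p0 | p1 | B | True 70% reads | True 40% reads |
|---|---|---|---|---|---|---|---|
| 10 | 2 | 0.3 | 1.50% | 2.96% | 0.990 | 70.3% | 40.6% |
| 10 | 2 | 3 | 1.50% | 2.96% | 1.028 | 69.2% | 38.3% |
| 30 | 4 | 0.3 | 4.50% | 15.86% | 0.918 | 72.5% | 44.9% |
| 30 | 4 | 3 | 4.50% | 15.86% | 1.208 | 63.7% | 27.5% |
| any | 1 | any | – | equal to p0 | 1.000 | 70.0% | 40.0% |
| any | any | 1 | – | – | 1.000 | 70.0% | 40.0% |

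Second row worked through: B = (1 + 0.0296 × 2)/(1 + 0.015 × 2) = 1.059/1.030 = 1.028, and 1 − 0.30 × 1.028 = 69.2%.

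The mid-range shift is under one point at a true VE of 70% and at most 1.7 points at 40%. The extremes need a high rate, a strong effect on vaccination and a strong effect on the outcome together. The sign turns on whether a past episode protects or marks higher risk.

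**The case against.** The strongest reply is that two years is the longest window any confounder needs, not a uniform rule. Several Table 2 items use one year, so a shorter window is not in itself a contradiction. Six months might be deliberate if immunity after an episode is thought to be short-lived, and the online supplement, which is not shown, may say so. Adjustment for healthcare-seeking, health status and treatment may absorb part of any effect, and Section 2.5.4 already discloses that zoster immunity is underestimated. Most of this limits the size of the point without removing it. The disclosure blames unattended infections and the data years, whereas for attended episodes in the previous two years the limit is the chosen window. A control outcome reveals bias only if it shares the omitted cause, and nothing in the article makes prior zoster a cause of urinary tract infection.

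A reader might infer more: that the zoster VE is certainly confounded, that the bias is larger in patients with MS, IBD or CIRD, and that the primary ratio is pulled down. One can construct such a case. Take a true VE of 60%, relative risk 3, and an episode 7 to 24 months ago in 6% of vaccinated people against 2% of controls. Then B = 1.12/1.04 = 1.077 and VE reads 56.9%. With 12% against 4% in the diseased, B = 1.24/1.08 = 1.148 and VE reads 54.1%, so the ratio is 0.541/0.569 = 0.95 when the truth is 1.00.

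The documents do not support that reading. The inputs imply about 13 and 27 attended episodes per 1000 per year in controls and vaccination odds ratios of about 3.1 and 3.3, alongside a harmful relative risk of 3, although the protocol describes the node as immunity. With a protective relative risk of 0.5 and the same proportions, B is 0.97/0.99 = 0.980 and 0.94/0.98 = 0.959. VE then reads 60.8% and 61.6%, and the ratio is about 1.01. Greater susceptibility to infection in the diseased groups does not by itself create a larger imbalance between vaccinated people and controls matched exactly on disease group.

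**Conclusion.** The point stands as an avoidable weakness in measuring a confounder that the protocol itself requires. Coding attended zoster 7 to 24 months before entry as none follows directly from the text, and 75% of the guaranteed window is affected. The constant-rate assumption is needed only to read this as a share of episodes.

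The consequence is that residual confounding of zoster VE may remain, with unknown direction. It is probably small under mid-range assumptions, reaches several points only in strong scenarios, and is nil if such an episode has no effect on vaccination or none on later zoster. An effect on the ratio of VE between diseased and non-diseased people cannot be ruled out, but nothing in the documents shows one. The change is worth making because it costs little, not because a large bias has been demonstrated.

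**What to change.** Extend the look-back for medically attended zoster to the full 24 months. The preferred form is time since the last episode in four categories: none, 0-6, 7-12 and 13-24 months. Enter it in the Cox model used for g-computation and in the entropy-balancing weights of the Kaplan-Meier sensitivity analysis. The six-month group stays as its own category, so nothing is lost if recent episodes are what matters, and the data can show whether older ones add anything.

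A simple 24-month indicator would also close the gap. If six months is intended, Section 2.5.4 should give the reason and list the window among the sources of underestimated immunity.

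The cost is two more model terms (three instead of one) and a rerun of the existing algorithm, ICD-10 code B02 with an antiviral prescription, over claims already held. No new data are needed. A further sensitivity analysis using all claims since 2013, in people insured throughout, is optional.
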